## Abstract

To date, there is a shortage of effective treatment strategies for Alzheimer’s disease (AD), and although repetitive transcranial magnetic stimulation (rTMS) can improve AD cognitive function, there are obvious individual differences, which may be related to different apolipoprotein E (APOE) genotypes. As the risk and pathogenesis of AD varies greatly among different genotypes precise treatment strategies should be implemented depending upon genotype, which has not been proved by clinical studies. Apart from that, the published clinical studies are highly heterogeneous, and therefore, systematic and well-developed randomized controlled Trails (RCT) and demonstration of precise administration protocols are required. To verify this hypothesis, this project designed a RCT study, and randomly divided apoE4 carrier AD and non-carrier AD into high-frequency rTMS (HF-rTMS) or low-frequency rTMS (LF-rTMS) treatment groups. Specifically, 80 patients with AD, namely 48 APOE4 carriers and 32 non-APOE4 carriers will be included in the study. After that, based on different stimulation frequencies of rTMS, they will be divided into the HF-rTMS group and the LF-rTMS group, when patients with AD will be randomly assigned to different treatment groups. After AD patients are involved in the study, their memory, cognition, anxiety, depression and activities of daily living will be tested before and during 2 weeks of rTMS. Furthermore, peripheral blood will be collected before and after treatment to detect changes in pathological indexes via MSD platform (Meso Scale Discovery), while 32-channel EEG data will be also collected to detect and analyze changes in gamma oscillation. In addition, these patients will be followed up for 6 months and their neuropsychological scale was also evaluated every month. At present, our study has included 18 AD patients (10 APOE4 carriers; 8 non-carriers). Our study is still in progress. The grouping has not been unblinded. But the preliminary data demonstrated that non-carriers had better MoCA score improvement than APOE4 carriers. The results indicated that the two populations of AD patients should be treated differently. Thus, this project will provide direction for precision rTMS in AD and also promotes a shift in relevant treatment philosophy.

**Clinical Trial Registration:** [www.ClinicalTrials.gov], identifier [ChiCTR2100041625].

## Introduction

Alzheimer’s disease (AD) is a neurodegenerative disease characterized by memory loss and cognitive dysfunction, with a very high prevalence in the middle-aged and elderly population. In this context, hundreds of billions of dollars have been invested in related research and development worldwide, but unfortunately, there are still no drugs with proven efficacy. Moreover, patients may wander and lose their ability to live in the late stages, which is a heavy burden for society and families (Zhou et al., 2019). Therefore, investigating new treatments is urgently needed.

Repetitive transcranial magnetic stimulation (rTMS) is a safe, non-invasive, and inexpensive neuromodulation that can affect the synaptic plasticity of neurons and enhance brain function by adjusting parameters such as stimulation frequency and stimulation intensity (Bestmann, 2008). In recent years, some researchers have tried to adopt rTMS to treat Alzheimer’s disease and found that it has a better therapeutic effect (Dong et al., 2018; Chou et al., 2020). The current clinical treatment of Alzheimer’s disease with medications has unsatisfactory therapeutic effect. Zhang et al. (2020) reported a meta-analysis of pharmacological treatments showing that improvement of Mini-mental State Examination (MMSE) score standard mean difference (SMD) ranges from −0.29 to 0.49; Lu et al. (2020) also reported another analysis of anti- Aβ agents for mild to moderate Alzheimer’s disease suggesting no effect of anti- Aβ drugs vs. the placebo group (SMD of MMSE score improvement: −0.29, 95% CI −0.76–0.17; SMD of ADAScog score improvement: MD: 0.20, 95% CI: −0.40–0.81). In contrast, Chu et al. (2021) reported a promising result. The patients who received high-frequency TMS treatment had a significant improvement in MMSE score (1.65, 0.77–2.54) when compared with sham TMS. In addition, Dong et al. (2018) report also supported the viewpoint that high-frequency rTMS led to a significant improvement in cognition as measured by ADAS-cog (MD = −3.65, 95% CI −5.82 to −1.48). Although the results derived from different study samples, their subjects were AD patients. Although there are no studies designed to compare the differences in therapeutic effects between drugs and rTMS, these data point to the possibility that rTMS is superior to drug therapy of AD patients.

Unfortunately, the results of the published clinical studies on transcranial magnetic stimulation greatly differ, with different parameters and stimulation targets being used, and a wide variation in stimulation patterns (Dong et al., 2018; Chou et al., 2020). Specifically, there are obvious individual differences in patient response to transcranial magnetic stimulation (Dong et al., 2018; Chou et al., 2020). Therefore, the precise implementation of transcranial magnetic stimulation therapy is crucial.

How to precisely direct the rTMS strategy is remains unsolved. However, recent studies indicate that APOE gene-typing is a possible candidate. The apolipoprotein gene (APOE) that can be classified into E2, E3, and E4 subtypes based on the differences in the bases encoding the rs429358 and rs7412 loci but falls into six genotypes according to the double allele typing. The different genotypes play different roles in the pathogenesis of Alzheimer’s disease. The APOE ε2 allele proven to be the strongest genetic protective factor but the APOE ε4 allele was the strongest genetic risk factor for Alzheimer’s disease after multiple large scale genome-wide studies (Serrano-Pozo et al., 2021). Several researchers have called for the study and treatment of carriers and non-carriers as different phenotypic groups (Yamazaki et al., 2019; Serrano-Pozo et al., 2021). In addition, the other researchers found that APOE ε4 allele carriers had a different outcome of physical exercise treatment (Cancela-Carral et al., 2021). Therefore, we speculate that different APOE ε4 allele carriers have different outcomes of rTMS.

Its potential mechanism may be related to impairment of the function of GABAergic interneurons (Knoferle et al., 2014; Lenz et al., 2016; Wang et al., 2018). Many studies have suggested that the APOE4 allele can reduce the number and impair the function of GABA interneurons in the brain and increased cortical excitability (Knoferle et al., 2014; Lenz et al., 2016; Wang et al., 2018). This feature can also be confirmed by EEG results. High-frequency gamma oscillations are generally encoded by GABA interneurons in the brain (Traub et al., 2003; Colgin et al., 2009; Buzsaki and Wang, 2012; Gillespie et al., 2016). Inhibition of this neuronal activity can lead to a reduction in gamma oscillations, and the reduction of gamma oscillations in the brain of APOE4 carriers (Traub et al., 2003; Colgin et al., 2009; Buzsaki and Wang, 2012; Gillespie et al., 2016) is closely related to the symptoms of AD (Zhao et al., 2018; Etter et al., 2019; Najm et al., 2019). Transcranial magnetic stimulation can improve gamma oscillation power and amplitude, and improve cognitive function (Barr et al., 2009). These results suggest that the damage to gamma oscillation activities caused by the APOE4 allele may affect the treatment results. In summary, it is clear that the APOE genotype determines the number and function of GABAergic neurons in AD patients, and therefore may be related to the heterogeneity of transcranial magnetic stimulation effects. Considering this background, transcranial magnetic stimulation treatment protocols being implemented should vary with APOE genotypes.

Previous studies have tested the effect of both high-frequency rTMS (HF-rTMS) and low-frequency rTMS (LF-rTMS). Interestingly, it was found that both HF-rTMS of the left dorsolateral prefrontal cortex (L-DLPFC) and LF-rTMS of right dorsolateral prefrontal cortex (R-DLPFC) exhibited significant therapeutic efficacy (Chou et al., 2020). Additionally, Ahmed et al. (2012) reported that LF-rTMS of L-DLPFC also showed significant therapeutic efficacy for mild to moderate dementia. But there are no uniform guidelines or standards to guide the choice of treatment protocol. In terms of experience, most doctors will choose high frequency as the treatment scheme. The present study will adopt the left dorsolateral prefrontal cortex (L-DLPFC) as the intervention target.

We believe that different APOE4 carriers should be given different treatment schemes than non-APOE4 carriers because of the excitability of their neural networks is different. The APOE4 carriers have increased network excitability due to the impairment of GABAergic interneuron function (Najm et al., 2019). Compared with the APOE ε3 allele, APOE ε4 allele increases Ca^2+^ excitability due to lysosome dysregulation and impaired modulation of Ca^2+^ responses upon changes in extracellular lipids (Larramona-Arcas et al., 2020). Traditional theory suggests that high-frequency rTMS increases cortical excitability by inducing long-duration enhancement potentials, while low-frequency rTMS decreases cortical excitability by inducing long-duration inhibition potentials (Pell et al., 2011). GABAergic neuronal receptor activity is mainly associated with chloride channel opening (Traub et al., 2003), and high-frequency stimulation is more likely to induce long-term potentiation (LTP) (Pell et al., 2011). Hence, high-frequency treatment contributes to more gamma oscillatory activity and better therapeutic effects. However, for APOE4 carriers with more significant loss of GABAergic neurons (Knoferle et al., 2014; Najm et al., 2019), HF treatment may be less effective. In this case, low-frequency therapy may be more suitable for that kind of patients. Therefore, in this study, it is believed that different transcranial magnetic stimulation regimens should be selected for AD patients based on APOE genotypes, so as to obtain precise treatment strategies.

In summary, this paper aims to study the difference in the efficacy of different rTMS strategies in AD patients with different APOE genotypes, and analyze the changes of gamma oscillations.

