**Inclusion criteria**

(1)The age ranges from 50 to 85 years old.(2)Subjective perception of memory loss more than 1 year; MMSE ≤ 26 (level of education more than 7 years: MMSE ≤ 26; level of education 1–7years: MMSE ≤ 24; level of education less than 1 year: MMSE ≤ 19).(3)MRI exhibits medial temporal atrophy (hippocampus, entorhinal cortex, amygdala); MTA visual evaluation scale ≥ 2.

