### Randomization and Allocation

#### Stratified Randomized Groups

In this study, 48 APOE4 carrier AD patients (APOE4-AD) and 32 non-APOE4 carrier AD patients (Non-APOE4-AD) will be recruited. Then, they will be assigned to the HF-rTMS group and the LF-rTMS group based on the stratified randomization method: 40 for the HF-rTMS group and 40 for the LF-rTMS group, while in subgroups, 24 patients will be assigned to in the APOE4-HF group, 24 patients will be assigned to the APOE4-LF group, 16 patients will be assigned to non-APOE4-HF group, and 16 will be assigned to the non-APOE4-LF group. The specific process is as follows: Our team members consist of quality control personnel, TMS therapy physicians, neuropsychological assessors and laboratory staff. Specifically, quality control personnel are responsible for quality control of study data and grouping randomization; TMS therapy physicians perform TMS treatment based on information from quality control personnel; neuropsychological assessors conduct neuropsychological assessments before, during and after treatment and follow-up; laboratory staff are in charge of blood sample processing and testing. In addition, the grouping randomization information will not be released by quality control personnel until the primary endpoint of the study has been met for all program participants at follow-up (Table 1).

The postadmission randomization process are performed by the quality control staff. Specifically, the admission sequence of APOE4 carriers and non-carriers was 1–48 and 1–32, respectively, and the admission numbers of carriers and non-carriers were randomized using Excel sheet randomization to assign them within the HF-rTMS and LF-rTMS groups, respectively. When the follow-up of all subjects reached the clinical trial endpoint, the project quality control staff and the project leader verified the grouping information for unblinding and summarized the project data for statistical analysis.

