### Results in Progress

Our study is still in progress. Our current data are the preliminary data of the RCT study, and the grouping has not been unblinded. We analyzed the demographic informatics of APOE4 carriers and non-carriers and the changes in cognitive function scores before and after 2 weeks of rTMS treatment. More detailed information was displayed in Supplementary Table 1.

To date, 18 patients with clinically diagnosed Alzheimer’s disease have been included and have received rTMS treatment for 2 weeks. Among them, ten were APOE4 carriers; eight were non-carriers, and there were no significant differences in age, education or gender (Table 2). They were randomly assigned to the high-frequency treatment group or the low-frequency treatment group. Because the study was not blinded, we could not know which subgroup they were assigned to. We could only analyze the overall treatment effect. According to our preliminary results, there was no significant difference in MMSE score, MoCA score except ADAScog (Supplementary Table 1) score between the two groups before and after treatment. When comparing the improvement rate of the two groups, there was a significant difference in the improvement of MoCA score between the two groups. For non- carriers, the MoCA score but not the MMSE or ADAScog score improved by 2.65 ± 3.15, while for carriers, it improved by 0.1 ± 1.7 (*t* = 2.164, *p* = 0.046, Figures 2A–C).

**TABLE 2 T2:** Characteristics of the study cohort.

	APOE4 carriers (*n* = 10)	Non-APOE4 carriers (*n* = 8)	*p*-value
Sex F/M	6/4	5/3	0.914
Age, years	70.37.45	73.756.27	0.312
Education level, years	7.72.98	6.135.37	0.44
MMSE score before rTMS	12.66.77	15.888.54	0.377
MoCA score before rTMS	7.94.28	9.255.50	0.566
ADAScog score before rTMS	39.1316.49	34.8719.03	0.618
MMSE score after rTMS	13.56.22	16.638.73	0.388
MoCA score after rTMS	84.47	11.887.72	0.202
ADAScog score after rTMS	37.1616.39	31.5721.21	0.536

*n, number; F, female; M, male; MMSE, Mini Mental State Examination; rTMS, repetitive transcranial magnetic stimulation; MoCA, Montreal Cognitive Assessment Scale; ADAScog, Assessment Scale-cognitive subscale.*

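### The between-genotype difference in the HF-LF effect is an observational contrast that disease stage could confound, and the plan neither estimates it nor checks it against baseline severity

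*Protocol article*

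**What the plan says.** **Purpose.** Under Objectives, the primary aim is to compare the efficacy of rTMS across APOE genotypes as a basis for precise treatment. The Introduction concludes that "different transcranial magnetic stimulation regimens should be selected for AD patients based on APOE genotypes".

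**Allocation.** Under Stratified Randomized Groups, "48 APOE4 carrier AD patients (APOE4-AD) and 32 non-APOE4 carrier AD patients (Non-APOE4-AD) will be recruited", and "they will be assigned to the HF-rTMS group and the LF-rTMS group based on the stratified randomization method". The cells are 24 HF and 24 LF carriers, and 16 HF and 16 LF non-carriers. Genotype is the only stratification factor named.

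**Eligibility.** The criterion reads "Subjective perception of memory loss more than 1 year; MMSE ≤ 26", with lower ceilings for less education. No minimum score is given.

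**Analysis.** Statistical Hypothesis sets an HF versus LF comparison in non-carriers, then one in carriers. It also gives a threshold for comparing the four subgroups. Statistical Analysis Methods names the t-test, repeated-measures ANOVA and the Wilcoxon rank sum test. Neither section describes an estimate of how much the HF-LF effect differs between genotypes, or a term for severity.

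**Data so far.** Table 2 (row "MMSE score before rTMS" and the MoCA and ADAS-cog rows) gives baseline values for 10 carriers and 8 non-carriers. The Discussion takes the preliminary carrier/non-carrier difference as grounds for treating the two groups differently and does not mention severity.

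**The concern.** Randomising frequency within each stratum makes HF and LF patients of the same genotype comparable. It does nothing to make carriers comparable with non-carriers. If the benefit of one frequency over the other depends on how advanced the disease is, and the strata differ in stage, separate tests by genotype will show a difference that looks like an APOE effect. The wide range of stages admitted leaves room for this.

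The article's own reasoning makes stage a rival explanation worth checking. The Introduction ties reduced gamma oscillation to AD symptoms and uses the same mechanism to explain why HF may work less well in carriers. Its citation for LF at this target is that "LF-rTMS of L-DLPFC also showed significant therapeutic efficacy for mild to moderate dementia", whereas eligibility is not limited to those stages.

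At stake is a rule for choosing frequency by genotype. If stage were the real driver, the rule could be wrong for mildly affected carriers and severely affected non-carriers. The baseline data needed to examine this are already being collected.

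**Working it through.** **1. Reproduce the baseline figure.** Inputs from Table 2: MMSE 12.6 (SD 6.77, n = 10) in carriers and 15.88 (SD 8.54, n = 8) in non-carriers.

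- Difference: 15.88 - 12.6 = 3.28.
- Pooled SD: sqrt[(9 × 6.77² + 7 × 8.54²)/16] = 7.60.
- SE: 7.60 × sqrt(1/10 + 1/8) = 3.60; t = 0.91 on 16 df; p = 0.376 (Table 2 gives 0.377).
- 95% CI: 3.28 ± 2.12 × 3.60 = -4.36 to 10.92.

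The other two scales also reproduce:

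| Scale | Carriers | Non-carriers | Difference (95% CI) | p |
|---|---|---|---|---|
| MoCA | 7.9 | 9.25 | 1.35 (-3.53 to 6.23) | 0.566 |
| ADAS-cog | 39.13 | 34.87 | -4.26 (-22.0 to 13.5) | 0.618 |

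Carriers are numerically worse on each scale, and every interval includes zero.

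**2. Range of severity.** The baseline MMSE SDs of 6.77 and 8.54 compare with 1.7 and 1.8 in the population cited under Sample Size Calculation. The enrolled range of stages is wide.

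**3. Size of a false genotype difference.** Let the HF-LF effect change by s MMSE points per baseline MMSE point. The documents give no value for s, so it is an assumption. With no true APOE effect, the apparent genotype difference is s × gap.

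| s | Gap 3.28 | Over the 95% CI of the gap |
|---|---|---|
| 0 | 0 | 0 |
| 0.1 | 0.33 | -0.44 to 1.09 |
| 0.2 | 0.66 | -0.87 to 2.18 |
| 0.3 | 0.98 | -1.31 to 3.28 |

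Given 18 patients, even the sign of the false difference is open.

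**4. Simulation at the planned size.** Settings: 48 carriers and 32 non-carriers split equally by frequency; baseline MMSE drawn from the Table 2 means and SDs and truncated to 0-26; residual SD sqrt[(1.9² + 2.3²)/2] = 2.11 from the sample-size inputs; no true APOE effect; 1,500 runs per setting. Both models contain baseline MMSE as a main effect.

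| s | False difference (absolute), no baseline-by-frequency term | Rejection at 5% | Rejection with the term |
|---|---|---|---|
| 0.1 | 0.30 | 5.9% | 5.0% |
| 0.2 | 0.56 | 8.9% | 5.5% |
| 0.3 | 0.86 | 11.5% | 4.5% |

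With the term, the bias is about zero. A main effect of baseline alone does not remove it. The bias is a little below step 3 because truncation shrinks the mean gap to about 2.86.

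**5. Cost in precision.** d = 3.28/7.60 = 0.43. With a 60:40 mix, r = 0.43/sqrt(0.43² + 1/0.24) = 0.207. The variance inflation is 1/(1 - 0.207²) = 1.045, so the standard error of the genotype-by-frequency estimate rises by a factor of 1.022.

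For an added age-by-frequency term, Table 2 gives ages 70.3 (SD 7.45) and 73.75 (SD 6.27), so d = 3.45/6.96 = 0.50. Both terms together raise the standard error by about 5%, or 4% to 7% for a within-group age-MMSE correlation between 0.3 and -0.3 (assumption).

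**6. Power for the genotype-by-frequency estimate.** SE = 2.11 × sqrt(2/24 + 2/16) = 0.96. Two-sided 5% power is about 69% for a 2.4-point difference and 23% for 1.2 points, before attrition or added terms.

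**The case against.** The strongest reply is that both links in the argument are unproven. A reader might infer from Table 2 that carriers enter with more advanced disease. The data do not support that: there are 10 and 8 patients, every interval spans zero, and three overlapping cognitive scales in the same 18 people are not three independent confirmations. A reader might also infer from the mild-to-moderate citation that the frequency effect depends on stage. The sentence reports efficacy in that population and says nothing about other stages or about HF by stage. Both points stand.

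It would also be wrong to set the 3.28-point gap against the 2.4-point design difference. The first is a baseline contrast between genotypes and the second a post-treatment contrast between frequencies. Only slope × gap is relevant.

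Two further points stand. HF versus LF within each genotype is randomised and unbiased, and choosing by genotype could be right on average for the recruited population without APOE being the cause. Severity may also lie on the pathway from APOE to response, so adjusting for it could remove part of a real genotype effect.

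Finally, covariates and sensitivity models are often left to an analysis plan that is not shown. Their absence is not the point here. The article itself sets ordered tests by genotype and already moves from a carrier/non-carrier difference to different treatment. That inference is not protected by the randomisation, whatever a later document adds.

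**Conclusion.** The point holds in a limited form. Attributing a difference between strata in the HF-LF effect to APOE is an observational inference that disease stage could confound. The within-genotype comparisons are not affected.

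The size is conditional. If the 3.28-point gap persisted and the slope were 0.1 to 0.3, the false difference would be about 0.3 to 1.0 MMSE points, and a 5% interaction test would reject about 6% to 12% of the time. With a zero slope or no gap there is no bias. The simulated rates also rest on a residual SD of 2.11.

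The documents do not show that confounding is present. They show that the design cannot exclude it and that the stated analysis would not reveal it. The check is cheap enough to be worth prespecifying.

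**What to change.** In Statistical Hypothesis:

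- Add an estimate of the genotype-by-frequency difference in MMSE with its 95% confidence interval. The two ordered tests do not supply one, so this means fitting a joint model across strata.
- Report that estimate without and with a baseline-MMSE-by-frequency term, as a prespecified sensitivity analysis. An age-by-frequency term is optional.
- Describe the APOE contrast as observational, and tabulate baseline severity by genotype.
- Do not make a recommendation depend on significance after adjustment. Power is too low for that, and severity may lie on the APOE pathway. If the estimate shrinks materially, state that genotype cannot be separated from disease stage.

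No new patients, data or change of treatment are needed. The cost is one joint model, a standard error for the genotype-by-frequency estimate about 2% wider with the MMSE term (about 4% to 7% if age is added), and possibly a more cautious conclusion.
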